## Abstract

Background: Social behavior is mediated by steroid hormones, whereby various lines of evidence indicate that metformin might improve the symptoms of social withdrawal. This directly yields to the aim of the study to correlate the impact of metformin treatment on the potential alterations in steroid hormone homeostasis, which is ultimately impacting social behavior. Therefore, urinary samples of patients before and after treatment with metformin will be correlated to social behavior to elucidate potential changes in steroid hormone profiles and social behavior. Material and Methods: An observational study in healthy adults with a new indication for metformin. Steroid hormone analysis, including the most prominent androgen, estrogen, progesterone, aldosterone, corticosterone, cortisone and cortisol metabolites analyzed with gas chromatography–mass spectrometry and a questionnaire on social behavior (Autism Spectrum Questionnaire (AQ)) will be administered prior to and after around a 12-week phase of metformin treatment. Discussion: It is likely that due to different pathophysiological mechanisms such as an effect on the respiratory chain in mitochondria or via AMP-activated protein kinase, a general alteration of steroid hormone levels can be detected prior to post treatment. The encompassing measurement of steroid hormones shall give hints concerning the involvement of specific cascades yielding potential pharmacological targets for future research.

## 1. Background and Need for This Study

The oral biguanide metformin has been an effective first-line treatment of type 2 diabetes mellitus in adults for more than 60 years. It is to this day the most prescribed oral antiglycemic drug in the world and remains the foundation of type 2 diabetes mellitus treatment, according to the American Diabetes Association, due to its safety, efficacy and cost-efficiency [1,2,3]. Metformin is a valid option when a first increased blood sugar level is detected; however, in the long run, it is not enough for patients suffering from diabetes, and these end up with other pharmaceuticals even with insulin therapy. Nevertheless, recent findings support the acutely decreased hepatic glucose production through a mild transient inhibition of the mitochondrial respiratory chain complex I as the main effect of metformin in reducing blood sugar levels. This reduced hepatic energy state leads to an activation of AMPK (AMP-activated protein kinase), further reducing gluconeogenesis in liver cells. The respiratory chain complex I is further supported as the main target by the preserved metabolic effect of metformin in liver-specific AMPK-deficient mice [4].

Surprisingly, studies have shown metformin treatment reduces macrovascular events and mortality in diabetes mellitus type 2 patients exceeding the expected risk reduction through decreased blood glucose levels. More recent studies have further shown strong support for additional benefits in treating obesity, metabolic syndrome, polycystic ovary disease and depression while also having anti-inflammatory and neuroprotective effects, opening up the possibility for new off-label indications [2,3,4,5].

First, treatment with metformin mimics some of the benefits of caloric restriction, yielding increased insulin sensitivity and reduced low-density lipoprotein and cholesterol levels while inhibiting low-grade inflammation [6,7,8,9,10].

Furthermore, AMP-activated protein kinase activity is increasing antioxidant protection, resulting in reductions in both oxidative damage accumulation and chronic inflammation [6,7,8,9,10,11]. The reduction of oxidative stress, present in several illnesses ranging from cancer up to neurodevelopment disorders with social withdrawal even in their most severe form as autistic diseases [12,13,14], could thus potentially be altered through metformin. To date, the etiopathogenesis or the biochemical basis of autism and neurodegenerative diseases has not been conclusively elucidated, and accordingly, the treatment options are not yet exhausted. Furthermore, we know from analyses of children with autism that there appears to be a change in the cholesterol-dependent steroid metabolism yielding to hyperandrogenism [15,16,17,18]. Causes might be increased oxidative stress resulting in the increased 17,20-lyase-catalyzing activity of adrenal P450c17 through p38α [12]. Interestingly, it was shown that P450c17 phosphorylation selectively increases 17,20-lyase activity and androgen biosynthesis [12]. In consequence, it was indicated that these actions may contribute to the beneficial effects of metformin not only on the reduction of oxidative stress and, in consequence, hyperandrogenism but more generally on the general health and lifespan [9,19]. Direct studies report an effect of metformin on the most famous androgen testosterone in a substantial manner, implying an interdependence of androgens and metformin [20,21]. Furthermore, it was shown that metformin inhibits testosterone-induced stress and unfolded protein response activation by suppressing p38 MAPK phosphorylation (one main cascade in mediating oxidative stress] [22]. These findings can be well embedded in altered kynurenine pathways yielding lower melatonin levels in affected subjects with autism [23,24]. As melatonin is considered to have a very potent antioxidative effect, this allows combining the findings of increased oxidative stress, mitochondrial dysfunction and altered steroid hormones in affected subjects with autism [24]. It was shown in a behavioral mouse model that metformin inhibited the androgen synthesis pathways while also influencing social behavior [19,25]. This might be due to alterations of steroid hormones as studies, for example, pointed to a relationship between testosterone and mainly dominance behavior; however, more recent research suggests that this relationship only holds for individuals with low levels of cortisol, implying that the sum of the metabolites modulates behavior but not the sole concentration of a single metabolite [26]. Furthermore, alterations of steroid hormones would be in line with a dysfunction of the autonomic nervous system (ANS) [27] and a dysregulation of the CRH-ACTH system in autism [28] (reviewed by Taylor and Corbett). This, in addition, directly allows linking steroid hormones via cytokines with inflammation showing the potential broad etiopathogenesis of autism [14].

Additionally, several lines of evidence indicate a beneficial effect of metformin on depression, neurodevelopmental disorders such as autism, neurodegenerative disorders such as Alzheimer’s disease and genetic diseases with neurodevelopmental consequences such as fragile X syndrome [4,29,30]. After only ten days of injection with metformin in a mouse model of Fragile X syndrome (one generally accepted cause of autism spectrum disorders), metformin improved autistic symptoms such as increased grooming and decreased socialization, and treated mice showed normal brain connections and behavioral patterns [31,32,33]. As individuals with autism have social impairments (e.g., a lack of social signal interpretation) and therefore an inability to interpret these signals to guide appropriate behaviors, metformin might be useful as it seems to have a protective effect on social withdrawal potentially mediated by steroid hormones [3,19,30,34,35].

To summarize, the effects of metformin on steroid hormones are, however, only partly elucidated (mainly restricted to the context of PCOS (polycystic ovary syndrome), yielding directly to the aim of this study [2,36,37,38,39,40,41,42,43,44,45].(Figure 1)

## 2. Hypothesis

Several lines of evidence indicate that metformin seems to have an effect on steroid hormones [38,42,46,47,48,49,50]. These studies mainly analyze the effects of metformin on androgen and estrogen markers. Although we already succeeded in showing the involvement of steroid hormones in social withdrawal and interaction with metformin [19], an encompassing analysis opening up possible therapeutic potential is missed. This directly yields to the aim of the study: to assess the effects of metformin on steroid hormones and social behavior. Therefore, we aim to measure steroid hormones from urine samples prior to and during treatment with metformin. Furthermore, we would also like to analyze the effects of metformin on social behavior; therefore, we intend to administer a questionnaire on social behavior to correlate potential alterations in steroid hormones and social behavior.

### 2.1. Primary Research Hypothesis

As a hypothesis with potential falsification, it shall be stated that a newly administered standard therapy with metformin has no influence on steroid hormone profiles in subjects having an indication for Metformin [38,42,46,47,48,49,50,51].

### 2.2. Secondary Research Hypothesis

As a hypothesis with potential falsification, it shall be stated that a newly administered standard therapy with metformin has no influence on social behavior in subjects having an indication for metformin [19,51].

There is no statistical correlation between steroid hormone levels and social behavioral changes [51].

## 3. Material and Methods

### 3.1. Trial Design

As we try to extend our research into the effects of metformin treatment not previously investigated (steroid hormone levels and social behavior), we intend to choose a simple study design.

The study is designed as a clinical trial to investigate changes primary in steroid hormones and secondary in social behavior during metformin treatment. Therefore, a baseline data set will be obtained prior to intervention, and a follow-up at 12 weeks will be conducted. An accompanying social environment anamnesis will also be collected.

The metformin indication itself is independent of study participation and is made following up-to-date diabetes guidelines. The study participation consists of urinary samples and a standardized Autism-Spectrum Quotient questionnaire obtained twice. All patient samples and data will be collected with prior informed consent.

### 3.2. Objectives

#### 3.2.1. Primary Research Objective

This study aims to analyze the effect of metformin treatment on steroid hormone profiles. Therefore, steroid hormones in patients with a new indication for metformin shall be measured with an encompassing gas chromatography–mass spectrometry (GC–MS) prior to treatment start and after 12 weeks of treatment.

#### 3.2.2. Secondary Research Objective

This study will investigate changes in social behavior under metformin treatment. Additionally, to the above-mentioned measurements, an autism questionnaire (Autism-Spectrum Quotient) [52,53,54] shall be conducted at both times. This questionnaire was chosen primarily due to its reliability, objectivity and validity in rapidly assessing the individual traits of an adult in the continuum from normality to autistic behavior, and additionally, the composer of the questionnaire Simon Baron-Cohen is directly addressing steroid hormones in his research [55].

This study will elucidate the potential correlation between steroid hormone levels and social behavioral changes.

### 3.3. Endpoints

#### 3.3.1. Primary Research Endpoint

Changes in steroid hormone profiles of interest (see below) prior to metformin treatment start and after 12 weeks of treatment.

#### 3.3.2. Secondary Research Endpoint

Changes in social behavior measured by the Autism-Spectrum Quotient AQ (see below) prior to metformin treatment start and after 12 weeks of treatment.

Correlation between steroid hormone profiles and social behavioral changes.

### 3.4. Eligibility Criteria

#### 3.4.1. Inclusion Criteria

Patients (male or female) older than 18 years with type 2 diabetes mellitus and an indication for metformin according to the American Diabetes Association, starting a new metformin treatment or are pausing treatment for example due to a further medical investigation for at least seven days. The main marker will be fasting plasma glucose levels of≥ 7.0mmol/L and/or HbA1c ≥ 6.5% [56].

#### 3.4.2. Exclusion Criteria

Patients under 18 years of age.Clinically significant concomitant disease (e.g., advanced renal failure, hepatic dysfunction, neoplasia).Significant musculoskeletal disease.Active infection during sample collection.Immunosuppressive medical therapy.Hormonal/steroid treatment.Pregnancy.Psychiatric disease and known social-behavior-altering medication (e.g., antipsychotic medication).Known or suspected malcompliance, drug or alcohol abuse.Inability to follow the procedures of the study, e.g., due to insufficient language skills, severe dementia.Life expectancy less than 6 months.Poor tolerability to metformin treatment with following treatment discontinuation within duration of follow-up.Pharmaceutical treatment with insulin or another pharmaceutical with a known strong effect on blood sugar levels.

### 3.5. Intervention and Follow-Up

In the 1980s, a correlation between insulin, insulin-sensitizing drugs (e.g., metformin) and androgens was already being implied [57]. In studies conducted on women with PCOS, a treatment duration of 6 weeks of metformin at a target dosage (1500mg daily) was deemed appropriate for a substantial effect on hormonal levels, with the results showing significant changes [41]. Therefore, we will be collecting the follow-up samples and data 12 weeks after treatment starts. As the treatment will be conducted by the treating physician, there might be differences between patients in metformin dosage during the saturation period before reaching target dosage. The 12-week follow-up will ensure a sufficient treatment time passed. Target dosage (500mg–3g per day) and saturation period will be according to the treating physician. The cumulative dosage received will be quantified for every patient enrolled to allow potential analyses for dosage-related effects (standardized for treatment duration).

To research the primary endpoint of steroid hormone profile changes, we will collect urinary samples prior to metformin treatment start and after 12 weeks of treatment. Similarly, to research the secondary endpoint of social behavioral changes, we will conduct a questionnaire (Autism-Spectrum Quotient) along with social environmental anamnesis at both times.

The additional medical risks of this study are to be assessed as very low (collection of urine samples along with a questionnaire during a patient interview). Risks arise only from the administration of metformin, which has to be assessed as a safe, very well-known and frequently used oral antiglycemic drug, the only severe side effect being lactic acidosis [1]. In general, metformin, which would have also been the first-line treatment without conducting the study, is a sensible choice for the treatment of type 2 diabetes mellitus [1].

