## 5. Statistical Analysis

Mean and SEM (standard error of mean) of all metabolites will be calculated pre-versus post intervention for the respective sub-samples distinguished by age and sex. To analyze the distribution patterns of the measured values of each metabolite Kolmogorov–Smirnov tests will be conducted. If normality distribution is present, the differences between pre-versus post intervention shall be analyzed with two-tailed dependent t-tests while correcting for multiple comparisons with Bonferroni correction. If the hypothesis of normal distribution must be rejected for metabolite concentrations pre-versus post intervention, Wilcoxon tests shall be conducted. If normal distribution is present, differences pre-versus post intervention will be further quantified with the calculation of effect sizes by Cohen with pooled standard deviation and 95% confidence intervals [63,64]. For metabolites not showing a normal distribution, effect sizes shall be calculated according to Pallant (2005) [65,66]. Correlation analysis (Pearson correlation coefficient) will be conducted to detect a potential relationship between cumulative metformin dosage (standardized for body weight and treatment duration] and steroid hormone concentrations, respectively, scores from the autism questionnaire. For female subjects before versus after menopause, analyses will be conducted separately. Potential differences will be compared with prior gained reference values from our lab [67]. As we do have a pool of healthy subjects, an individually pairwise matched design (twin matching) might be another possibility to reduce an age bias increasing the validity of the results [67].

Based on these preliminary analyses, structure equation modeling can be applied if indicated in order to combine findings from biochemical analysis and from questionnaires. All calculations will be performed with GraphPad Prism (GraphPad Software, Inc., La Jolla, CA, USA) and SPSS (Microsoft Inc., Redmond, WA, USA).

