## 6. Discussion

The aim of this study is to analyze the effects of metformin treatment on steroid hormone profiles. To the best of our knowledge, there is no study directly elucidating the presumed effects on steroid hormones and social behavior in humans [19]. The description of potential steroid hormone alterations will allow making different statements concerning pathway activities such as, for example, enzymes involved. However, we will not be able to understand the complexity of all steroid hormone pathways [68]. Characterizing the ligands will allow to descriptively develop an understanding; however, as ligand binding induces specific conformational changes in the ligand-binding domain, which can modulate surface topology and protein-protein interactions between androgen receptors and coregulators, resulting tissue-specific gene regulation processes cannot be fully captured with this descriptively oriented analysis [68].

We are aware that the optimal study design would be a placebo-controlled crossover trial, which is, however, for practical reasons, impossible to conduct. Nevertheless, several lines of evidence suggested the involvement of steroid hormones in autism, especially increased androgens [15]. Just recently, a meta-analysis and systematic review performed by us showed higher androgen levels in hand with increased 17/20 lyase activity in children with autism [66]. Furthermore, the involvement of glucose homeostasis factors such as insulin and growth hormone is likely [69]. Males with Asperger’s syndrome showed altered levels of 24 biomarkers, including increased levels of cytokines and other inflammatory molecules [69]. We know from our own analyses of children with autism spectrum disorders that those affected show a substantial change in steroid hormone profiles [16,18]. In our mice model, we were able to show a change in social behavioral patterns, including social withdrawal, after receiving metformin treatment [19]. These findings are to be expanded with a clinical focus and tested in humans. Thereby, as steroid hormones may exert different effects on the brain, respectively cognitive functions such as learning, emotional judgment or face recognition, the findings might have a high value from a translational point of view [70,71].

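### The planned dose correlation is unadjusted although physicians choose the metformin dose, so it can show or hide a dose gradient if dosing follows severity or indication

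*Protocol article*

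**What the plan says.** Section 3.5 opens its dosing sentence with "Target dosage (500mg–3g per day" and ends it with "saturation period will be according to the treating physician". The dose is therefore neither randomised nor set by the protocol, and targets may differ six-fold (3000/500) between patients. The same section gives the purpose of the dose record: "The cumulative dosage received will be quantified for every patient enrolled to allow potential analyses for dosage-related effects".

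Section 5 turns that possibility into a planned analysis: "Correlation analysis (Pearson correlation coefficient) will be conducted to detect a potential relationship between cumulative metformin dosage", scaled by body weight and time on treatment, on one side, and steroid concentrations and questionnaire scores on the other. No glycaemic marker and no indication enters. The only related safeguard in Section 5 is that women before and after menopause are analysed apart.

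Two other places matter:
- Section 3.4.1 makes glycaemia the eligibility measure ("The main marker will be fasting plasma glucose levels" above a threshold, and/or HbA1c).
- Section 3.6 adds patients whose indication is PCOS rather than type 2 diabetes.

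**The concern.** A bivariate correlation cannot separate the dose from the reasons for the dose. If patients with worse glycaemia, or with one of the two indications, tend to receive more drug and also tend to have different steroid or AQ values, the coefficient picks up that difference. This is confounding by indication. Scaling dose by weight and duration does not remove it, and neither does splitting women by menopausal status.

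The trial has no control group; Section 6 names a placebo-controlled crossover as the best design but one that cannot be run here. A dose gradient is then a result that readers may readily take as evidence that metformin itself acts. The error can also go the other way and cancel a true gradient.

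**Working it through.** **Inputs from the protocol.** Dose at the physician's discretion, 500 mg to 3 g per day (Section 3.5). Unadjusted Pearson correlation (Section 5). About 45 patients to analyse (Section 4.4) and about 100 expected from recruitment (Section 3.6). A Bonferroni level of 0.001136 = 0.05/44 (Section 4.4).

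**The plan's own figure.** The protocol gives no figure for the dose correlation, so 45 serves only as the setting. It can be approximated. The testosterone fall is 2.7 − 2.0 = 0.7. Take 0.3 and 0.2 as SDs and assume a pre/post correlation of 0.5. The SD of differences is then √(0.09 + 0.04 − 0.06) = 0.265, so d = 2.65 and a quarter of that is 0.66. A two-sided paired t-test at 0.001136 with 80% power needs 44. The result depends on the assumed correlation: 77 at 0, and 31 at 0.7.

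**Assumptions for the check.** Severity S correlates a with dose and b with the outcome, and dose has no effect. The documents give no value for a or b.

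**Step 1: spurious correlation.** Under this model the expected correlation of dose and outcome is r = a × b.

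**Step 2: chance of a significant result.** By Fisher's z, with m = atanh(r) × √(n − 3), the two-sided 5% rejection probability is Φ(m − 1.96) + Φ(−m − 1.96). With a = b:

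| a = b | r | m, n = 45 | Chance, n = 45 | m, n = 100 | Chance, n = 100 |
|---|---|---|---|---|---|
| 0.3 | 0.09 | 0.58 | 9% | 0.89 | 14% |
| 0.4 | 0.16 | 1.05 | 18% | 1.59 | 36% |
| 0.5 | 0.25 | 1.66 | 38% | 2.52 | 71% |

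The nominal rate is 5%.

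**Step 3: check by simulation** (20,000 runs per setting). At a = b = 0.3 and 0.5 the rates are 9% and 38% for n = 45, and 15% and 72% for n = 100. With unequal links, a = 0.5 and b = 0.3, they are 17% and 32%. The partial correlation given S rejects in 4.7% to 5.1% of runs. It does so because S is here the whole confounder and is measured without error.

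**Step 4: stricter level.** Section 5 states Bonferroni for the t-tests only. If 0.05/44 were also applied to the correlations, the simulated rates for a = b = 0.3 and 0.5 are 0.4% and 4.9% at n = 45, and 0.9% and 23% at n = 100, against a nominal 0.11%. Correction lowers the rates but does not remove the bias.

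**Step 5: hiding a gradient.** With a true standardised dose effect β and severity effect γ, the marginal correlation is β + aγ. At a = γ = 0.5 a true β of −0.25 gives −0.25 + 0.25 = 0.

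**Step 6: change scores.** Write the outcome as c₀S + e₀ before and c₁S + e₁ after treatment. The change is (c₁ − c₀)S + e₁ − e₀. If severity shifts both values equally (c₁ = c₀), the severity term drops out and so does the bias. It stays only if severity predicts the 12-week change. Section 5 speaks of concentrations and scores and does not say that changes are meant.

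**The case against.** Several points on the other side stand.

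- **Dosing by severity is not stated.** A reader might infer from Section 3.5 that sicker patients get more drug. The text says only that the physician decides, and the one dose difference it explains is during the run-up to the target. The exclusions in Section 3.4.2 (insulin and other strong glucose-lowering drugs, advanced renal failure, stopping for intolerance) plausibly narrow the range of severity.
- **The link to the outcome is thin.** A reader might take "the involvement of glucose homeostasis factors such as insulin and growth hormone is likely" in Section 6 to mean that glycaemia drives steroid levels. That sentence stands in a discussion of factors involved in autism and does not say so. What remains is Section 3.5, which reports that a correlation of androgens with insulin and insulin-sensitising drugs was implied in the 1980s.
- **Change scores help.** It is tempting to say that the bias survives them in any case. Step 6 shows that it needs a further assumption, for which the documents give no evidence.
- **The analysis is peripheral and cautiously worded.** Dose-response is in no hypothesis, objective or endpoint. Section 3.5 says "to allow potential analyses for dosage-related effects", Section 5 says "to detect a potential relationship between cumulative metformin dosage", and Section 7.1 classes the study as exploratory. Nowhere is a gradient announced as proof of a drug effect.
- **The marker may not be complete.** Eligibility allows glucose and/or HbA1c, PCOS patients may have neither, and patients who paused metformin for as little as seven days may have baseline values already affected by treatment.

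One objection does not stand: that covariates may be left to an unseen analysis plan. The article does not leave the method open; it names a plain Pearson coefficient and says that it will be conducted.

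**Conclusion.** The point holds as a conditional one. The stated method cannot separate dose from the reasons for it, and dose is not assigned independently of the patient. Whether bias arises depends on two links that the documents do not establish: that severity or indication guides dosing, and that it relates to the outcome (to its change, if change scores are used).

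Under assumed links of 0.3 to 0.5, the false-positive rate of a single 5% test is about 9% to 38% at n = 45 and 14% to 71% at n = 100. The upper figures need 0.5 on both links and no correction for multiplicity, and should not be read as an expected rate for this trial.

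The consequence is limited to a supportive analysis. The primary pre/post comparison does not use dose and is unaffected. Usual-care dosing is itself no error; the weakness lies in the Pearson sentence of Section 5.

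**What to change.** Change Section 5 only:

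- Replace the plain Pearson correlation by a regression of within-patient change on cumulative dose, or by the corresponding partial correlation.
- Adjust for one baseline glycaemic marker, chosen in advance: HbA1c or fasting glucose, whichever is available for most patients. Do not substitute one for the other, since they are on different scales.
- Adjust also for indication (type 2 diabetes or PCOS).
- State that any gradient will be reported as an exploratory association and not as a dosage effect of metformin.

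The cost is one or two degrees of freedom (one per covariate) and the loss of patients without the chosen marker. Residual confounding remains, for example by tolerability or by severity that one marker does not capture, so the reporting statement is needed even after adjustment. Dosing, visits and sample size stay as they are.
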